### Planned Statistical Analysis

All data will be prepared and analyzed using the latest version of Python [72] and the libraries NumPy [73], Pandas [74], and scikit-learn [75] or equivalent statistical packages. A notebook containing the analysis in documented code will be made available on Open Science Framework [76] for research transparency following the analysis.

#### Data Cleaning and Preparation

We will transform categorical variables into a format suitable for numerical analysis. For binary categorical variables, we will use label encoding. For multinomial variables, we will apply one-hot encoding. In addition, for ordinal data, which have a natural order, we will transform the categories into integers.

Predictor variables with over 20% missing data will be excluded from the analysis. Categorical variables exhibiting low variance, as determined by predictors with <5% of a certain response will be removed. For instance, by removing the variable “Sleep medication” if it only occurs in 3 out of 300 patients. This approach aims to reduce unnecessary complexity in the predictions and to minimize the risk of overfitting. To control for multicollinearity, variables with a correlation coefficient ≥0.8 will be removed from the traditional prediction analysis but will be retained for the ML model development. Data that are highly skewed will be transformed if deemed appropriate.

Cognitive test results will be manually reviewed before model fitting to validate a proper result. Comments pertaining to technical difficulties and disturbances that may have affected the test result will be assessed by two of the authors and lead to exclusion if so judged. Participants who have noted during screening that Swedish is not their native language will be excluded from the analysis for CERAD and FAS. We will standardize the raw scores from the cognitive tests using normative regression models with age, education and sex as covariates. This standardization process will convert raw scores into *Z* scores, as previously described by Franke Foyen et al [62] and for a full overview of the multiple linear regression models used and how they were calculated, see the studies by Mindmore [77] and van den Hurk et al [78].

Patients who have missing data for the posttreatment PSS-10, ie, the missing outcome variable for the primary aim, will be replaced by a PSS-10 process measurement at week 10 if available; If not, the patient will be excluded from the analysis. The number of participants excluded from the final models will be described.

To prepare our primary outcome, RCI for the PSS-10 before to after treatment will be computed using the following formula [39]:

Cronbach α=0.83 from normative data will be used [38]. Patients exhibiting an RCI of −1.96 will be classified as responders.

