### Outcomes

The primary outcome in this study and the original RCT is PSS-10 [35]. The PSS-10 is a self-report questionnaire developed to evaluate an individual’s perception of life as unpredictable, uncontrollable, and overwhelming. Responses are recorded on an ordinal scale ranging from 0 n*ever* to 4 *very often*, reflecting the individual’s feelings and thoughts over the past month. It contains statements, such as ‘*In the last month, how often have you been upset because of something that happened unexpectedly?’* and sum scores range from 0 to 40. The PSS is the most commonly used outcome measure of stress-management interventions globally [8,36,37]. For this study, a Swedish version of the PSS-10 was used. The PSS-10 has been found to exhibit high internal consistency (Cronbach α=0.84) and adequate construct validity [38]. The PSS-10 was administered digitally through the web-based study platform before randomization to treatment, every 3 weeks during the treatment phase, and at treatment completion (12 weeks). During treatment, the instructions for the PSS-10 were modified to have patients consider the last week instead of the last month. For this study, the sum score of the PSS-10 will be dichotomized into responder or nonresponder after treatment based on the RCI criteria [39] to differentiate between statistically significant change and those attributable to measurement error or natural variability. The PSS-10 baseline and 3-week measurement will also be used as predictors.

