**3-week measurement**					
	SMBQ cognitive weariness	Burnout	Continuous		0-7
	SMBQ exhaustion	Burnout	Continuous		0-7
	SMBQ listlessness	Burnout	Continuous		0-7
	ISI	Insomnia severity	Interval		0-28
	PSS-10	Perceived stress	Interval		0-40

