#### Self-Rated Symptoms

*Alcohol use* was assessed using the Alcohol Use Disorder Identification Test [40,41]. This 10-item screening instrument evaluates alcohol consumption, drinking behavior, and alcohol-related problems over the past year. It contains items, such as *How often do you have six or more drinks on one occasion*? rated on various ordinal scales, typically ranging from 0 to 4.

*Symptoms of anxiety* were measured using the Generalized Anxiety Disorder-7 scale [42]. This screening tool assesses generalized anxiety symptoms over the past 2 weeks. It comprises 7 items, such as *not being able to stop or control worrying* rated on a 4-point ordinal scale ranging from 0 *not at all* to 3 *nearly every day*.

*Symptoms of burnout* were measured using the Shirom-Melamed Burnout Questionnaire [43,44]. It aims to measure 3 components of burnout; emotional and physical fatigue, cognitive weariness, and listlessness and contains statements such as *I have difficulty concentrating* rated on a 7-point scale ranging from 1 *never or almost never* to 7 *always or almost always* with some items using reversed scoring.

*Symptoms of depression* were measured using Montgomery-Åsberg Depression Rating Scale [45]. It is a 9-item questionnaire used to measure different aspects of depression such as concentration difficulties, suicidal thoughts, sadness, and affected appetite with answers rated on a 7-point ordinal scale from 0 to 6.

*Symptoms of exhaustion disorder* were measured using the 9-item Karolinska Exhaustion Disorder Scale [46]. Measuring different aspects of exhaustion such as fatigue, endurance, and sleep impairment, answers are rated on an ordinal scale from 0 to 6 (eg, ability to concentrate; ranging from 0 “I do not have any difficulty concentrating, and can read, watch TV and converse normally” to 6 “I cannot concentrate on anything at all*.*”)

*Functional disability* was measured using The World Health Organization Disability Assessment Schedule (2.0) [47], developed to assess functioning in the last 30 days in 6 different life domains, including cognition, mobility, self-care, relationships, life activities, and societal participation. It contains statements, such as “I have difficulty standing for longer periods such as 30 minutes.” Answers are rated on a 5-point ordinal scale ranging from 0 *never* to 4 *extreme or unable*. A 12-item version was used.

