#### Model Interpretation

The models developed to identify the responder status will be evaluated using BACC, precision and recall, both in the training set obtained through k-fold cross-validation and in the test set. Predictor importance in the RF model will be determined using Scikit-learn’s Feature importance function, which quantifies each predictor’s contribution to the model’s balanced classification accuracy. Area under the curve will be used to assess the models’ capability to distinguish between classes accurately. The approach will aim to provide a clear understanding of the models’ effectiveness and the role of various predictors. Our primary outcome of interest for comparison will be BACC in each model in the test set with the aim that (1) the model should perform better than a dummy model that simply predicts the most common responder status, and (2) that the model should perform 67% BACC or above to be deemed clinically useful [28]. Furthermore, the models will be statistically compared using bootstrap sampling. Specifically, we will generate 5000 bootstrap samples from the test set, calculating the BACC for each model on each sample. The distributions of these bootstrap BACCs will be compared and we will conclude that there is a statistically significant difference between models if the CIs do not overlap.

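### Random-forest importance is read one column at a time while some constructs enter as several correlated columns, so burnout in particular can look less important than a variable measured once

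*Protocol article*

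**What the plan says.** In the protocol article, *Data Cleaning and Preparation* sets the collinearity rule. Predictors whose correlation reaches the 0.8 cut-off "will be removed from the traditional prediction analysis but will be retained for the ML model development".

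Table 1 lists the predictors. SMBQ has three subscales under self-rated symptoms, and the same three recur in the week-3 block (for example "SMBQ cognitive weariness"), which makes six burnout columns. *Self-Rated Symptoms* describes the instrument: "It aims to measure 3 components of burnout; emotional and physical fatigue, cognitive weariness, and listlessness". ISI appears at both times. For perceived stress, *Outcomes* states: "The PSS-10 baseline and 3-week measurement will also be used as predictors". Age, educational attainment and treatment credibility have one row each.

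*Model Interpretation* takes random-forest importance from "Scikit-learn’s Feature importance function, which quantifies each predictor’s contribution to the model’s balanced classification accuracy". The stated purpose is to "provide a clear understanding of the models’ effectiveness and the role of various predictors". That section mentions neither grouping of related columns nor a caution about them. The main criterion for the ML models is BACC in the test set.

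**The concern.** When several columns carry much the same information, a forest can split on any of them, and the credit for the construct is divided. Under a permutation measure, the columns left intact also stand in for the shuffled one. A list of single-column importances therefore reflects how often a construct was measured as well as how much it predicts.

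This matters because importance is the plan's tool for explaining which predictors play a role. *Strengths and Limitations* also points to feature-importance metrics as the way to make the forest interpretable. Burnout severity, with six columns, could appear below a variable that predicts no better but was measured once, and a reader could draw the wrong conclusion about symptom severity.

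**Working it through.** **Inputs from the plan.** There is no planned figure for importance to reproduce. The plan gives N=300 and a 70/30 split, so 0.7 × 300 = 210 training and 0.3 × 300 = 90 test patients. With the 10% attrition expected in the RCT, 270 remain: 189 and 81. Columns per construct come from Table 1: six for SMBQ, two each for PSS-10 and ISI.

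**Assumptions.** The documents report no correlations between predictors and no effect sizes, so these are assumed and varied.

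**Measures.** BACC = (sensitivity + specificity)/2. Permutation loss = test-set BACC minus test-set BACC after shuffling the column, or after shuffling all columns of a group together. Impurity importance is the forest's built-in per-column value. Both were examined: the plan's description fits a permutation measure scored on BACC, but the built-in forest value is impurity-based.

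**Check 1: equal true effects.** Construct A is measured by k columns, A_j = √r·L + √(1−r)·e_j. Construct B is measured once with the same reliability. The log-odds of response are L + M, where L and M are the two latent constructs. There were 40 noise columns, 300 trees and 40 replicates.

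| k | r | Impurity A per column / B (ratio) | Permutation loss A per column / B (ratio) | A permuted as a group | B above every A column (impurity) | BACC |
|---|---|---|---|---|---|---|
| 1 | 0.8 | 0.098 / 0.104 (0.94) | 0.057 / 0.070 (0.81) | – | 55% | 0.626 |
| 2 | 0.8 | 0.079 / 0.102 (0.77) | 0.047 / 0.061 (0.77) | 0.106 | 67.5% | 0.654 |
| 2 | 0.9 | 0.084 / 0.113 (0.74) | 0.038 / 0.067 (0.57) | 0.101 | 65% | 0.672 |
| 6 | 0.8 | 0.050 / 0.085 (0.59) | 0.007 / 0.047 (0.15) | 0.134 | 72.5% | 0.666 |
| 6 | 0.9 | 0.049 / 0.091 (0.54) | 0.004 / 0.042 (0.10) | 0.120 | 75% | 0.665 |

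The k=1 row is the baseline and shows the simulation noise. Two columns move the ratios a little; six move them a lot, above all under permutation. The ranking percentages are rough: with 40 replicates the standard error near 50% is √(0.25/40) = 0.079.

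**Check 2: unequal effects.** Construct A has log-odds 0.8 per SD, the single predictor 0.5, with 189/81 patients and six columns at r=0.8. Per-column permutation loss fell from about 0.089 with one column to 0.004 with six. The weaker predictor outranked every A column in 10% of runs with one column and 30% with six. Joint permutation ranked the stronger construct first in 95%. A separate run of 60 replicates gave 27% (one column), 23% (two) and 35% (six). Its rise of 8 points from one column to six is within simulation error: √(0.27×0.73/60 + 0.35×0.65/60) = 0.084.

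**Check 3: is the 0.8 threshold the cause?** In the same 0.8 versus 0.5 setting with 30 noise columns, the weaker predictor's impurity importance relative to the average severity column was 0.76 with one column, 1.10 with six at r=0.8 and 1.26 with six at r=0.65. Permutation loss per severity column was 0.051, 0.006 and 0.009 respectively. Dilution is present when no pair reaches 0.8. The one-column loss differs between this run and Check 2 (0.051 against about 0.089), so the sizes are indicative.

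**Check 4: type of comparator.** With equal effects and six columns at r=0.8, a 9-level ordinal comparator gave impurity 0.040 per column against 0.051 and permutation loss 0.003 against 0.027. An 11-level one gave 0.040 against 0.050 and 0.002 against 0.025. With a dichotomised comparator the impurity order reverses (0.049 against 0.035), while permutation loss still favours the single column (0.010 against 0.021). With two columns against a dichotomised comparator, neither measure shows the problem (impurity 0.080 against 0.035, permutation 0.049 against 0.027).

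**Check 5: does grouping over-correct?** In Check 1 two equally predictive constructs scored 0.134 (six columns, grouped) and 0.047 (one column), a ratio of 0.134/0.047 = 2.9. Part of that is real, since six columns measure the latent construct better than one. With log-odds 0.5 for the six-column construct and 0.8 for the single predictor, grouped permutation wrongly put the six-column construct first in 37.5% of runs, against 20% with one column.

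**The case against.** The strongest reply is that this concerns a secondary, descriptive output. The ML models are judged on test-set BACC, and the extra columns did not lower it in Check 1 (0.626 with one column, 0.666 with six). The hypothesised predictors are also examined by univariate logistic regressions (*Predictor Analysis*), which other columns cannot dilute. All of that stands. It does not supply a construct-level reading, because the ablation step also measures each predictor's unique contribution.

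A reader might infer that keeping variables correlated at 0.8 or more is itself the mistake. The documents do not support that: the rule serves prediction, and Check 3 shows sharing at lower correlations too. A reader might also infer that burnout will look unimportant. In Check 1 with six columns at r=0.8, the diluted columns still had impurity importance 0.050 against 0.015 for average noise, so they are diluted, not lost. Nor do the hypotheses set an order among age, education, severity and credibility; they are listed together.

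Two further objections have force. Table 1's repeat measures are not shown to be near-duplicates: the SMBQ subscales are described as separate components, and the PSS-10 recall period changes from a month to a week during treatment. Grouping also has its own tilt (Check 5) and would hide the difference between pretreatment status and early course if it replaced the per-column values.

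**Conclusion.** The point holds in limited form. Reading importance column by column, with repeat measures of a construct kept in the model, can make burnout look less important than an equally or less predictive variable measured once. In simulation the effect is strong for six columns: the per-column permutation loss was 0.15 times that of an equally predictive single column, and impurity importance 0.59 times. For two columns, as with PSS-10 and the two ISI scores, it is mild. Ranking errors also occur with one column (10% and 27% in the two runs of Check 2), so only the excess can be put down to duplication, and that excess is imprecisely estimated.

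All sizes rest on assumed correlations and effect sizes. Test-set BACC, the retained predictor set and the univariate regressions are not in question. This is a cheap improvement to the interpretation of one model.

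**What to change.** Leave the models and predictors as they are. Add to *Model Interpretation* a pre-specified grouped permutation importance for the random forest: shuffle all columns of a Table 1 construct together in the test set and report the loss in BACC, beside the per-column values and not in place of them. Fix the assignment of columns to constructs in a table beforehand (for example, all six SMBQ columns; both PSS-10 scores; both ISI scores). Report the number of columns in each group, since grouped loss tilts towards larger groups, and state that single-column ranks are not construct ranks.

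The cost is one mapping table, a little extra code, and less detail within a construct in the grouped result. The article says the data had not been analysed for this study as of March 2025, so at that date the grouping could still be set before results were seen.

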#### Descriptive Statistics

Descriptive statistics will be used to summarize the sample characteristics and pretreatment variables, including mean or median, SDs and IQR for continuous variables, and proportions for categorical variables.

#### Predictor Analysis

For the traditional regression analysis, data will be imputed using the KNN imputer. The imputer, a nonparametric imputation method, works by imputing missing values based on the k-nearest neighbors; in this study *k* will be determined by cross-validation. It uses the Euclidean distance metric to find the nearest neighbors and can be used for both numerical and categorical data. Each missing value is imputed using values from its k-nearest neighbors. After imputation, we will run univariate logistic regressions for each predictor listed in Table 1 using RCI as a target variable. Predictors that are statistically significant in the univariate analyses will then be included in an ablation study, a systematic approach to evaluate feature importance. This method involves iteratively removing each significant predictor from a full model, measuring the change in explained variance, and then reinserting it, thereby quantifying each predictor’s unique contribution to the model’s explanatory power in the context of all other features.

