### Objective of the Study

The overall objective of this study is to predict treatment outcomes in patients with stress-related disorders. Due to limitations in existing methods for prediction analyses, this study aims to first evaluate putative predictors using a traditional prediction paradigm, and second to model treatment outcomes using an ML approach. Our primary outcome of interest is responder status after treatment on the Perceived Stress Scale-10 (PSS-10), evaluated using the reliable change index (RCI; further described in the Planned Statistical Analysis and Data Cleaning and Preparation sections). On the basis of earlier research on predictors of treatment outcome, we hypothesize that key predictors will include younger age, education level, baseline symptom severity, treatment credibility, and history of sickness absence. Furthermore, we anticipate that the ML models will outperform a dummy model predicting the majority class and achieve a BACC of ≥67%, thus being indicated clinically useful [28].

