## Methods

### Study Design

We will use collected data from a randomized controlled trial (RCT; N=300) of internet-delivered CBT for patients diagnosed with AD or ED compared to an active, internet-delivered control condition consisting of general health-promoting advice. A priori power analysis conducted for the main outcome in the RCT indicated that 300 study participants would be needed for a 90% power to detect a between-group effect size of Cohen *d*=0.4 with a significance level of .05 and an expected attrition rate of 10%. Due to the limited sample size and general lack of knowledge on predictors of treatment effect, prediction models in this study will be based on pooled data from both treatment arms. The study design is prospective, and predictors will include sociodemographic and clinical information, clinician-assessed data, self-rated symptoms, and results from cognitive test scores. The results will be reported in line with the TRIPOD+AI (Transparent Reporting of a Multivariable Prediction Model for Individual Prognosis or Diagnosis+Artificial Intelligence) statement [30].

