### Putative Predictors

#### Overview

Predictors were gathered through self-report measures that were administered in the web-based study platform, clinical assessment conducted before inclusion to the study, and remote cognitive testing. Table 1 presents all predictors included in the study.

**Table 1 table1:** Putative predictors of treatment outcome in stress-related disorders

Predictor		Construct measured	Type	Clinician-rated	Scoring range

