#### Clinical Characteristics

During the clinical interview, patients reported their medication regimen, specifying both the number (0-4) and type of medication (antidepressants, anxiolytics, sleep medication, and pain medication and yes or no). Primary diagnosis (AD or ED), and possible secondary psychiatric diagnosis (eg, anxiety or depressive disorder) was assessed by the clinician using Mini International Neuropsychiatric Interview, self-rated ED (ordinal categories ranging from *no* to *yes—to a high degree*) [32], and the ADNM-8 [33]. Using ADNM-8, the patient was asked about which specific stressors had been present in the past 2 years (in 16 options, eg, *too much or too little work* or *financial difficulties*). The clinician assessed the length of the current episode (in months), and the age of the patients first episode (in years). Sick-leave status upon inclusion in the study (0%-100% in 5 steps), length of current sick-leave episode (*0-1 months* to *>12 months* in 5 categories) was self-reported.

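### Up to 58 predictors are screened by univariate significance with no stated multiplicity control, and the survivors' contributions are then measured in the same patients, so false entries and optimistic values are to be expected

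*Protocol article*

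**What the plan says.** All references are to the protocol article.

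- **Screen.** Under Predictor Analysis, after nearest-neighbour imputation, "we will run univariate logistic regressions for each predictor listed in Table 1 using RCI as a target variable". The Overview of the putative predictors says that "Table 1 presents all predictors included in the study".
- **Selection and measurement.** "Predictors that are statistically significant in the univariate analyses will then be included in an ablation study". Each survivor is dropped from the full model in turn, and the loss of explained variance is read as its unique contribution. No significance level, multiplicity correction, hold-out or resampling is given for this step.
- **Safeguards elsewhere.** The 70/30 split (Train Test Split), five-fold cross-validation (Hyperparameter Tuning) and 5000 bootstrap samples of the test set (Model Interpretation) are all described for the machine learning models.
- **Filters.** Data Cleaning and Preparation removes variables with more than 20% missing data, categorical variables with under 5% in a response and, for the traditional analysis, variables correlated at 0.8 or above.
- **Hypotheses.** Under Objective of the Study, "we hypothesize that key predictors will include younger age, education level, baseline symptom severity, treatment credibility, and history of sickness absence". Predictor Analysis treats these no differently from the other rows. The sick-leave items described under Clinical Characteristics are "Sick-leave status upon inclusion in the study (0%-100% in 5 steps), length of current sick-leave episode".

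**The concern.** The first aim is to identify predictors of response. Significance alone decides which variables reach the ablation, and the same patients then supply the estimate of how much each one matters. A variable that passed by chance passed because its association in this sample happened to be large, so its measured contribution is biased upward. This follows from selecting and then measuring in the same data, and it holds at any significance level.

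Two consequences follow. The predictor list may contain chance findings that carry a non-trivial apparent effect. The Discussion also wants to compare the traditional and machine learning approaches, but one side would report in-sample explained variance and the other held-out performance. In addition, a hypothesised predictor that narrowly misses significance gets no ablation estimate, while a noise variable can get one.

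**Working it through.** **1. The plan's own figure.** Study Design sizes the parent trial for "90% power to detect a between-group effect size of Cohen *d*=0.4", "with a significance level of .05 and an expected attrition rate of 10" per cent. Per arm: 2 × (1.960 + 1.282)² / 0.4² ≈ 131.4, so 132. Total 264, and 264 / 0.90 = 293.3, so 294. This agrees with 300 to within 2%. It concerns the comparison of arms; no error rate or power is stated for the predictor screen.

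**2. Number of tests.** Rows of Table 1: 10 sociodemographic + 19 clinical + 15 self-rated + 5 at week 3 + 2 treatment-related + 7 cognitive = 58.

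**3. False positives if all are null.** The two-sided 5% level is an assumption. The expected number is 0.05 × m, and for independent tests the chance of at least one is 1 − 0.95^m.

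| Tests m | Expected false | P(at least one) |
|---|---|---|
| 58 | 2.9 | 94.9% |
| 50 after filters | 2.5 | 92% |
| 40 after filters | 2.0 | 87% |
| 30 after filters | 1.5 | 79% |

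**4. Departures from that setting, varied one at a time.**
- Real predictors: with 5, 10 or 20 real ones among 58, the remaining nulls give 2.65, 2.4 or 1.9 expected false entries and 93%, 91% or 86%.
- Correlation: the expected number does not depend on correlation (about 2.9 in every simulation). The chance of at least one falls to 91% (moderate blocks), 86% (strong blocks), 84% (0.3 between all pairs) and 65% (0.5 between all pairs). These structures are assumed; 40,000 draws each.
- One-hot columns tested singly: four variables with 3, 8, 11 and 16 levels give 58 − 4 + 38 = 92 columns, hence 4.6 expected and 99%.

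**5. What the ablation reports on pure noise.** I simulated the screen and the drop-one step with 58 independent null predictors, 400 replicates per setting. Assumptions: n = 270 (300 less 10%) or 300; responder rate 30%, 40% or 50%; Nagelkerke R² as the measure. Means are over replicates in which at least one predictor was selected.

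| n | Apparent R² of selected model | Unique R² per false predictor |
|---|---|---|
| 270 | 0.081-0.085 | 0.025-0.026 |
| 300 | 0.071-0.079 | 0.023-0.024 |

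The true value is 0. The 5th to 95th percentile of the apparent R² runs from about 0.02 to 0.16. Applied to fresh data, the same models have a deviance R² of about −0.04 to −0.05. With moderately correlated predictors (n = 270, 40% responders) the figures are 0.071 and 0.019, and −0.045 in fresh data.

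**6. Mapping the hypotheses to Table 1.** Age, educational attainment and treatment credibility have one row each. Sickness absence has two: status and duration. Baseline symptom severity is not tied to particular rows among the 15 self-rated ones. No row records absence before the current episode.

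**The case against.** Four points can be made for the plan.

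- **Silence is not a decision.** The article says only that predictors must be significant. The .05 belongs to the parent trial's power calculation, and the level and any correction may be fixed in a fuller plan. This stands: a reader might infer an uncorrected 5% rule, but the text does not state one. It does not rescue the sequence that is stated, because selecting and then measuring in the same patients inflates the result at any level. Confining the step to the 70% training set would not help either, since selection and measurement would still share patients.
- **The worst case is not this dataset.** A reader might infer that false predictors are near certain. That needs all 58 rows tested, all null and all independent. The filters will remove some rows. The symptom scales overlap, several being measured twice. Some predictors are probably real, since the outcome is change in PSS-10 and baseline PSS-10 is itself a predictor. This stands, and it turns 95% into a range.
- **Sickness absence is measured.** A reader might infer that this hypothesis cannot be tested. Table 1 has two rows labelled with that construct, so it can be. Only the word history does not match, because both items describe the current situation.
- **The analysis is exploratory in spirit.** The Introduction concedes that single predictors are usually too weak to guide care, and the Discussion asks for external validation before clinical use. This limits the harm. It does not make the reported contributions unbiased.

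**Conclusion.** The concern holds in a limited form. The select-then-measure sequence is written into the plan and makes the ablation values optimistic. At an assumed two-sided 5% without correction, roughly 1.5 to 3 false entries should be expected. The chance of at least one is about 80-95%, or about 65% if all predictors are strongly correlated. Filters and correlation acting together could lower that chance further, and testing one-hot columns singly would raise it.

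The R² figures describe pure noise and rest on the assumed sample size and responder rate, which the article does not give. They show the scale of the bias and do not forecast the result. The sickness-absence point is a mismatch of wording. The article reports that the data had not been analysed for this study as of March 2025, so on that account the rule could still be changed without knowledge of the results.

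**What to change.** 1. State the significance level and control the false discovery rate across the univariate screen, for example Benjamini-Hochberg at 5%, with one joint likelihood-ratio test per multi-category variable. For scale, a Bonferroni level of 0.05 / 58 = 0.00086 would cut the expected false entries from 2.9 to 0.05; false discovery control is less strict once real predictors are present.
2. Report the ablation changes as optimism-corrected values from a bootstrap that repeats imputation, screening and the drop-one step in every sample. Label any uncorrected values as apparent, and do not set them beside the machine learning models' held-out results.
3. Name the Table 1 rows that represent the hypothesised predictors, including which symptom scales stand for baseline symptom severity. Enter these in the ablation model whatever their p-values.
4. Reword the sickness-absence hypothesis to sick-leave status at inclusion and duration of the current episode.

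The cost is wording and a little more code. Fewer predictors will be called significant, and the reported contributions will be smaller.
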